**ADL**			
	Katz ADL	0-6 points	
	IADL^e^	0-8 points	

^a^ADL: activities of daily living.

^b^DASS: Depression Anxiety Stress Scale.

^c^mRNA: messenger ribonucleic acid.

^d^WHOQOL-BREF: World Health Organization Quality of Life Brief Version.

^e^IADL: Instrumental Activities of Daily Living

Cognitive assessment will include the baseline scales and follow-up at 12 months. The scoring is shown in Table 13.

**Table 13 table13:** Cognitive assessment scoring.

Timeline and scales			Scoring
**Baseline**			
	MOCA^a^	0-30 points: executive function (0-5 points), naming (0-3 points), memory (0-5 points), attention (0-6 points), calculus (0-3 points), language (0-3 points), orientation (0-6 points), abstractization (0-2 points)	
	MIS^b^	0-15 points	
	BDST^c^	0-14 points	
	FDST^d^	0-16 points	
	TMT^e^-A	0-100 seconds (101 seconds means failed test)	
	TMT-B	0-300 seconds (301 seconds means failed test)	
	DSST^f^	Absolute number of correct answers (maximum 90 correct answers), absolute number of incorrect answers (maximum 90 incorrect answers)	

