### Procedures and Examinations

Clinical procedures and examinations will be performed in a silent room so there is no disturbance to both examiner and participant. Participants will receive information about each test that will be conducted. The scales and questionnaires used in the study are listed in Table 5.

**Table 5 table5:** Scales used in the study.

Objective	Scales
Assessment of IBD^a^ severity	HBI^b^ for patients with CD^c^ and SCCAI^d^ for patients with UC^e^
Assessment of quality of life	Romanian WHOQOL-BREF^f^ questionnaire
Assessment of depression, anxiety, and stress	Romanian DASS^g^-21
Cognitive assessment	Romanian MOCA^h^ 7.1, TMT^i^-A and TMT-B, backward digit testing, forward digit testing, DSST^j^
Assessment of COVID-19	Short COVID-19 questionnaire
Assessment of ADL^k^	IADL^l^ scale, Katz ADL scale

^a^IBD: inflammatory bowel disease.

^b^HBI: Harvey-Bradshaw Index.

^c^CD: Crohn’s disease.

^d^SCCAI: Simple Clinical Colitis Activity Index.

^e^UC: ulcerative colitis.

^f^WHOQOL-BREF: World Health Organization Quality of Life Brief Version.

^g^DASS: Depression-Anxiety-Stress Scale.

^h^MOCA: Montreal Cognitive Assessment.

^i^TMT: Trail Making Test.

^j^DSST: Digit Symbol Substitution Test.

^k^ADL: activities of daily living.

^l^IADL: Instrumental Activities of Daily Living.

The Montreal Cognitive Assessment (MOCA) 7.1 scale includes the Trail Making Test (TMT), drawing, long-term memory testing, verbal fluency tests, short-term memory recall testing, calculus, and spatial and temporal orientation questions. The maximum score obtained is 30 points. The normal range is ≥26 points. An additional point is given to patients who have an education level of ≤12 years.

The memory impairment score (MIS) is derived from the MOCA scale. The maximum score is 15 points. It derives from the short-term memory recall test. Subjects have to recall 5 words to gain points. If they recall the words spontaneously, 3 points are awarded for each word. If any clue is provided, 2 points are awarded if the word is recalled. If variants are provided, 1 point is awarded if the word is recalled. No point is awarded if the word is not recalled.

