The TMT involves the subject drawing a trail between 2 points, with the entire operation being timed. It has 2 different parts, TMT-A and TMT-B. TMT-A involves drawing a continuous line between numbers. TMT-B involves drawing a continuous line, alternating letters and numbers. An example of the test is provided before each part. TMT-A has a maximum time of 100 seconds, and 101 seconds means the subject has failed the test. TMT-B has a maximum time of 300 seconds, and 301 seconds means the subject has failed the test.

The Digit Symbol Substitution Test (DSST) involves the subject changing some numbers to symbols as specified in the legend of the test. A training zone is first created. If the training is completed, the subject is given 90 seconds to complete as many substitutions as possible. Correct and incorrect answers are counted.

In forward digit span testing (FDST) and backward digit span testing (BDST), the subject must recall the numbers provided by the examiner in forward order and then in backward order. FDST involves strings of numbers ranging from 2 to 8 numbers, and BDST involves strings of numbers ranging from 2 numbers to 7 numbers. Each string has 2 different variants, and the subject must make a maximum of 1 mistake in these variants, otherwise the test ends.

The Depression-Anxiety-Stress Scale (DASS) is a scale that includes 21 questions split into 3 categories (depression, stress, and anxiety), with 7 questions per category, the questions being interleaved. Each question has a score from 0 to 3, and the result is multiplied by 2.

The Harvey-Bradshaw Index (HBI) and the Simple Clinical Colitis Activity Index (SCCAI) are used for screening the subject. In this study, they are part of the inclusion criteria.

The quality-of-life instruments available in Romania are limited; therefore, the World Health Organization Quality of Life Brief Version (WHOQOL-BREF) will be used in order to determine the quality of life of our participants. The Instrumental Activities of Daily Living (IADL) is an 8-item scale that includes some instrumental daily activities, and it is a useful and essential tool for differentiating MCI from dementia. The Katzl ADL scale is a 6-item scale that includes casual daily activities and is also a useful and essential tool for differentiating MCI from dementia.

A blood sample will be obtained from each participant.

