**HBI^a^ (0-4 points=remission; 5-7 points=mild disease; 8-16 points=moderate disease; >16 points=severe disease)**			
	General health	Very well (0), slightly below par (1), poor (2), very poor (3), terrible (4)	
	Abdominal pain	None (0), mild (1), moderate (2), severe (2)	
	Liquid or soft stools on the previous day	Absolute number (1 point for each)	
	Abdominal mass	None (0), dubious (1), definite (2), definite tender (3)	
	Complications	Arthralgia (1), uveitis (1), erythema nodosum (1), aphthous ulcer (1), pyoderma gangrenosum (1), anal fissure (1), new fistula (1), abscess (1)	

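### Printed scoring rules conflict: MOCA domain maxima add to 33 under a 0–30 total, digit-span maxima do not fit the described test, and HBI scores moderate and severe pain alike

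*Protocol article*

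**What the plan says.** **MOCA.** Table 13 (Baseline) gives "0-30 points: executive function (0-5 points), naming (0-3 points), memory (0-5 points), attention (0-6 points), calculus (0-3 points"), followed by "language (0-3 points), orientation (0-6 points), abstractization (0-2 points"). The same list is repeated at 12, 24, 36 and 48 months. The Procedures and Examinations section states: "The maximum score obtained is 30 points. The normal range is ≥26 points".

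**Digit span.** The same section says "FDST involves strings of numbers ranging from 2 to 8 numbers, and BDST involves strings of numbers ranging from 2 numbers to 7 numbers", with two variants of each string. Table 13 gives 0–16 for the forward test (FDST) and 0–14 for the backward test (BDST), at baseline and again at 48 months.

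**HBI.** Table 10 scores abdominal pain as "None (0), mild (1), moderate (2), severe (2"). It defines remission as 0–4 points and mild disease as 5–7. Procedures and Examinations calls the HBI part of the inclusion criteria, although Table 2 sets no HBI threshold.

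**The concern.** These are operative scoring rules. The Abstract names MOCA and both digit-span tests as primary clinical outcomes, and the power calculation rests on MOCA. The HBI is the disease-activity score for the Crohn's disease patients.

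A data manager who builds the database from Table 13 as printed gets a MOCA total that can exceed its own stated maximum. For digit span, the text and the table imply tests of different length. For HBI pain, two named levels cannot be told apart.

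At stake are the classification of individuals against the MOCA limit of 26, the validity of the digit-span range, and, for some Crohn's disease patients, the split between remission and mild disease.

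**Working it through.** **Control checks on neighbouring scales.** Two other maxima in the article do reproduce, so the mismatches are specific to the items below.
- Memory impairment score: 5 words × 3 points = 15 (stated 0–15).
- Simple Clinical Colitis Activity Index: 3 + 2 + 3 + 3 + 4 + 5 = 20 (stated 0–20).

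**MOCA.** Inputs are the eight domain maxima in Table 13: executive 5, naming 3, memory 5, attention 6, calculus 3, language 3, orientation 6, abstraction 2.
- Sum: 5 + 3 + 5 + 6 + 3 + 3 + 6 + 2 = 33. Stated maximum: 30. Excess: 3.
- Leaving out one domain at a time gives 28 without executive, 30 without naming, 28 without memory, 27 without attention, 30 without calculus, 30 without language, 27 without orientation and 31 without abstraction.
- Three domains therefore restore 30. Calculus is the natural candidate, because it could be a component of attention. Arithmetic alone does not exclude naming or language.

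Consequence if all eight items were summed and calculus is the duplicate: recorded total = true total + calculus score (0 to 3). The limit of 26 is then reached from
- 23 with 3 calculus points (23 + 3 = 26),
- 24 with at least 2 (24 + 2 = 26),
- 25 with at least 1 (25 + 1 = 26).

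**Digit span.** Inputs are the string lengths and the two variants per string from Procedures and Examinations. Assumption: one point per correct string, since the article gives no points rule.
- FDST: lengths 2 to 8 are 7 lengths; 7 × 2 = 14. Stated 16, excess 2.
- BDST: lengths 2 to 7 are 6 lengths; 6 × 2 = 12. Stated 14, excess 2.
- The stated maxima equal 2 × 8 and 2 × 7, as if lengths began at 1. From a start at 2, they would need strings up to 9 and 8 digits (8 × 2 = 16 and 7 × 2 = 14).

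**HBI pain.** The levels score 0, 1, 2, 2. The other graded HBI items rise at every step (general health 0 to 4, abdominal mass 0 to 3). If the two upper pain levels are meant to differ by one point, a patient with severe pain and a printed total of 4 (remission) would total 5 (mild disease).

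**Power calculation.** It uses only a mean difference of 2, SD 3.0, α of .05, 80% power and the 2:1 ratio implied by 52 cases and 26 controls. With the normal approximation, controls = (1 + 1/2) × 3² × (1.960 + 0.842)² / 2² ≈ 26.5, so 27 controls and 54 cases. Power at the stated 26 and 52 is 0.793, so the plan's figures reproduce closely. No item maximum enters the formula.

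**The case against.** The strongest reply is that these are loose table entries. The MOCA total and its limit agree with each other wherever they appear. The article names an existing form (Romanian MOCA 7.1), and reading calculus as part of attention gives exactly 30. Nothing says that totals are built by adding the Table 13 items. A double count would also apply to both groups, so in a comparison of means it largely cancels, apart from any group difference in the duplicated item. The digit-span conflict depends on an unstated points rule. A tie between two HBI levels is not an arithmetic error.

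Most of this stands, and it limits the point. It does not remove it: the domains are printed as separate items with no sign of nesting, at all five time points in Table 13. A shift common to both groups does not cancel when individuals are classified against a fixed limit of 26.

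Four stronger readings are tempting and are not supported:
- **That MOCA scores already collected are inflated.** No section shows how totals were formed.
- **That inflation of up to 3 points undermines a study planned on a difference of 2.** The power calculation does not use the domain list.
- **That two different digit-span forms are used at different visits.** Table 13 gives the same ranges at baseline and 48 months; the conflict is between text and table.
- **That patients were wrongly admitted because of the HBI tie.** Table 2 gives no HBI threshold, and the article does not say that the two levels should differ.

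**Conclusion.** The printed scoring rules are inconsistent in two places and doubtful in a third.

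- **MOCA:** the listed maxima exceed the stated total by 3. This is certain as long as the items are read as separate, as printed. The effect on scores, up to 3 points, is conditional on totals having been summed from the list. That calculus is the duplicate is likely but unproven.
- **Digit span:** both stated maxima are 2 points, or one string length, above what the described test yields at one point per correct string.
- **HBI pain:** the item cannot separate moderate from severe. This is probably a misprint. It matters at the 4/5 boundary only if the levels are meant to differ.

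The sample size is unaffected. The correction should be made because the rules govern primary outcomes, the consequence is unknown until the records are checked, and the cost is small.

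**What to change.** 1. **Table 13, MOCA.** Show the duplicated item as a non-additive sub-item of its parent domain, after confirming against the form which item it is. State that the analysed total is the form total, maximum 30, at every visit where MOCA is given.
2. **Digit span.** Make Procedures and Examinations and Table 13 agree on the form actually used: string lengths, points per string and resulting maxima.
3. **Table 10, HBI.** Reconcile the abdominal pain item with the instrument form used.
4. **Record check before the intermediary analysis.** For the 103 participants reported as enrolled (53 + 50), look for MOCA totals above 30 and for totals equal to the sum of all eight listed items. Allow for the extra point given for 12 or fewer years of education. Check digit-span scores above 14 (forward) and 12 (backward), and the code used for severe HBI pain. Re-score only where the check shows that the printed table was used.

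The cost is three text or table corrections and one database query on 103 records. No new data collection or change to the sample size is needed.

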**Methods:**

A case-control study will be conducted on at least 100 patients diagnosed with IBD, matched with 100 healthy individual controls. The matching will include sex, age, and education. Patients will be fully examined, and a full interview and a neurological and cognitive examination will be performed. The primary clinical outcomes will be cognitive test scores (Montreal Cognitive Assessment, Trail Making Test, Digit Symbol Substitution Test, forward and backward digit span testing). Depression, stress, and anxiety screening will also be performed. Blood samples from all participants will be collected, and aliquots will be immediately stored in a biobank. Primary laboratory outcomes will include serum levels of presumed cognitive dysfunction blood biomarkers SAA, Hcy, S100B, and BDNF. Follow-up will be performed at 12, 24, 36, and 48 months.

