**Results:**

Data collection started in December 2021 and is ongoing. So far, 53 patients with IBD have been recruited and 50 HC matched. Data collection should end in January 2030. Intermediary analysis will be performed in April 2024. We expect patients with IBD to have lower scores on cognitive testing and a positive correlation between disease length and cognitive impairment level. In addition, the levels of stress, anxiety, and depression should be higher in the IBD group. The serum levels of the 4 biomarkers could correlate or anticorrelate with cognitive scores and serve as predictive factors for MCI or dementia development. A higher level of education, a younger age, the absence of malabsorption, and good disease control might serve as protectors against MCI.

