**48-month follow-up**			
	MOCA	0-30 points: executive function (0-5 points), naming (0-3 points), memory (0-5 points), attention (0-6 points), calculus (0-3 points), language (0-3 points), orientation (0-6 points), abstractization (0-2 points)	
	MIS	0-15 points	
	BDST	0-14 points	
	FDST	0-16 points	
	TMT-A	0-100 seconds (101 seconds means failed test)	
	TMT-B	0-300 seconds (301 seconds means failed test)	
	DSST	Absolute number of correct answers (maximum 90 correct answers), absolute number of incorrect answers (maximum 90 incorrect answers)	

^a^MOCA: Montreal Cognitive Assessment.

^b^MIS: memory impairment score.

^c^BDST: backward digit span testing.

^d^FDST: forward digit span testing.

^e^TMT: Trail Making Test.

^f^DSST: Digit Symbol Substitution Test.

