### Power Calculation, Statistical Model, and Data Analysis

Based on previous studies, the power of the study, with an α of .05 and a power of 80%, the required number of cases and controls is 52 and 26, respectively, for a mean difference in 2 points (SD 3.0) in MOCA scales.

Statistics will be computed using IBM SPSS software version 28.0.1 or newer. Descriptive analysis of the baseline characteristics of the overall population by gender, age, and education will be conducted. Continuous variables will be presented as the mean (SD) or the median (IQR), and countable data will be presented as numbers and percentages. Comparisons of groups will be conducted using the t-test or the Wilcoxon rank-sum test based on the type of distribution of data and the homogeneity of the variance. The chi-square test or the Fisher exact probability method will be used for counting data, as appropriate.

Multiple linear and logistical regression analyses will be performed to evaluate the association between outcomes and potential risk factors identified in the questionnaires. Participants lost to follow-up will be treated as right-censored data. The Pearson coefficient will be used to assess the correlation between cognitive scores and serum levels of the studied biomarkers. A 2-sided significance level of .05 will be used for all primary and secondary analyses unless stated otherwise.

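### DSST errors are scored as a raw count over a self-paced 90 seconds, so the error score mixes speed with accuracy and favours the slower group at equal accuracy (minor)

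*Protocol article*

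**What the plan says.** Under Procedures and Examinations, after a training step, "the subject is given 90 seconds to complete as many substitutions as possible". The next sentence adds: "Correct and incorrect answers are counted". Table 13 turns this into two scores at baseline, "Absolute number of correct answers (maximum 90 correct answers), absolute number of incorrect answers (maximum 90 incorrect answers", and repeats the rule at the 48-month visit, including "absolute number of incorrect answers (maximum 90 incorrect answers". It defines no error proportion and makes no adjustment for items attempted.

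The abstract states: "The primary clinical outcomes will be cognitive test scores", and lists the DSST among those tests. On direction, the authors write: "We expect patients with IBD to have lower scores on cognitive testing". The analysis section says: "Comparisons of groups will be conducted using the t-test or the Wilcoxon rank-sum test". It names no denominator or offset for any count.

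**The concern.** In a self-paced test the number of items attempted is also the number of chances to make an error. That number differs between people. It differs systematically between groups if one group is slower, which is a natural way for the expected lower scores to arise on a timed test.

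A raw error count compared between groups then answers a mixed question: how fast, and how accurate. At equal accuracy the slower group makes fewer errors and looks better. With a modest loss of accuracy the two effects can cancel. Read beside a lower number correct, the result could suggest that IBD patients are slower but more careful, when their accuracy is the same or worse. The same mixing would carry into change from baseline and into biomarker correlations if the raw error count were used there.

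**Working it through.** **The plan's own figure.** The only computed figure is the MOCA sample size: difference 2, SD 3.0, α .05, power 80%, two cases per control. Controls needed = 1.5 × (1.960 + 0.842)² × 3² / 2² ≈ 26.5, so 27 controls and 54 cases after rounding up. The stated 26 and 52 give 79.3% power by the normal approximation, so the figure reproduces to within rounding. It has no bearing on the DSST.

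**Inputs from the article.** A 90-second self-paced test; two absolute counts, each with a maximum of 90; at least 100 participants per group; two-sided .05; t-test or rank-sum test.

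**Assumptions (not in the article).** Controls attempt 60 items on average; error rates per item are 3-6.5%; the SD of attempts is 10 or 12, as stated below.

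**Break-even.** Let A be items attempted and e the error rate per attempt. Expected errors = A × e. The IBD group shows fewer expected errors when

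e(IBD) / e(HC) < A(HC) / A(IBD),

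the same number at equality, and more errors above it.

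- 60 v 50 attempts: break-even ratio 60/50 = 1.2.
- 60 v 40 attempts: break-even ratio 60/40 = 1.5.

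**Bias at equal accuracy.** With e equal, the ratio of mean counts equals the ratio of attempts. So 10%, 15% or 20% fewer attempts means 10%, 15% or 20% fewer errors, whatever the error rate.

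**How often that produces a false result.** Simulation with 100 per group, attempts SD 12, equal accuracy, two-sided rank-sum test. The cells give the share of studies with significantly fewer errors in IBD (nominal 2.5%). Everyone within a group has the same error rate.

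| Fewer attempts in IBD | Error rate 3% | Error rate 6% |
|---|---|---|
| 10% (54 v 60) | 15% | 25% |
| 15% (51 v 60) | 30% | 48% |
| 20% (48 v 60) | 49% | 74% |

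Repeat runs agree to within a few points, the highest being 77%. When error rates also vary between people (beta-binomial, coefficient of variation 1.0, again an assumption), the false rates fall to between about 7% and a little over 20%. The per-attempt proportion stays near nominal throughout. The bias in the mean count does not change.

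**Masking, reversal and detection.** Simulation with 100 per group, attempts SD 10, t-test, common error rate within each group:

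- HC 60 × 3% = 1.8; IBD 50 × 3.6% = 1.8. Rate ratio 1.2 equals the break-even, so the loss is masked. The count shows IBD worse in 2% of studies, the proportion in 41%.
- HC 60 × 3% = 1.8; IBD 40 × 4% = 1.6. Rate ratio 1.33 is below 1.5, so the loss is reversed. The count is significantly lower in IBD in 19%, the proportion significantly higher in 72%.
- HC 60 × 3% = 1.8; IBD 50 × 5% = 2.5. Rate ratio 1.67 is above 1.2, so the loss shows. The count detects it in 92%, the proportion in nearly 100%.

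With 48 attempts at 5% against 60 at 4% (SD 12, rank-sum test), mean counts are 2.4 and 2.4. The count finds the loss in about 2% of studies and the proportion in 61%. With the extra between-person variation, the contrast shrinks to about 2% against 15%.

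**Number correct.** Across these scenarios the number correct was significantly lower in IBD in about 89-100% of runs.

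**The case against.** The strongest reply is that Table 13 only records what is counted and the range it can take. Nowhere does the article say that the incorrect count will be tested alone or read as accuracy. Both counts are kept, so items attempted can be recovered for every participant, and the choice of a derived accuracy score could sit in an analysis plan that is not shown. This stands as far as intent goes: a reader might infer that the authors mean to treat the count as accuracy, and the text does not say so. It does not remove the point. Table 13 itself fixes the absolute number as the score, at both visits, for a test listed as a primary outcome, and the stated group comparisons have no denominator.

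A reader might also infer that a slower group always shows fewer errors, or that the DSST deficit itself would be hidden. Neither follows. The first fails above the break-even ratio: at 52 v 60 attempts with 6% v 4% errors, the count shows IBD significantly worse in about 80% of simulated studies. The second fails because the number correct falls with both slowness and error.

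The size is also open to challenge, fairly. With SD 12, 20% fewer attempts is a deficit of 12/12 = 1.0 SD, against the 2/3 = 0.67 SD planned for MOCA, in a cohort screened to exclude many causes of impairment. At 0.67 SD with between-person variation in accuracy, the false rate is about 11-12%.

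**Conclusion.** The point holds in a limited form, as a minor one. The DSST error score as written mixes speed with accuracy. If IBD patients attempt fewer items, it is biased towards fewer errors in IBD at equal accuracy, by the same percentage as the shortfall in attempts. It can mask or reverse a loss of accuracy up to the break-even ratio, and not beyond it. The problem is confined to the error part of the test and to the split between speed and accuracy. The DSST as a primary test is not invalidated.

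The direction is arithmetic and needs no outside figure. The frequency of a false finding of fewer errors, roughly 7-77% for 10-20% fewer attempts, rests wholly on assumed attempts, error rates and between-person variation. Its width shows how little the article pins down.

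**What to change.** In Table 13, keep the number correct as the DSST score. Replace the raw incorrect count as an analysed score by incorrect / (correct + incorrect), or model the errors with a binomial or overdispersed count model using log(attempted) as offset. Apply this at baseline and at the final DSST visit, which Table 4 places at 36 months and Table 13 at 48 months. Use the same form wherever errors enter change scores or biomarker correlations.

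The cost is a line or two of scoring and analysis wording. No new data are needed and the sample size is unaffected. The one downside is that simple proportions are noisy in people who attempt few items; the binomial or offset model gives those participants appropriate weight.
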